### Participants

A minimum of 96 patients initiating dialysis will be recruited into the study. The type of dialysis is haemodialysis, peritoneal dialysis or home dialysis, or collectively known as ‘dialysis’. The following criteria must be met for inclusion in the study: (1) diagnosis of near ESKD confirmed by medical records; (2) expected to commence maintenance dialysis for the first time in the next 3 months or commencement of dialysis in the past 3 months; (3) aged 18 or above; and (4) able to converse in English without an interpreter. Exclusion criteria are: (1) presence of developmental disability or amnestic syndrome impairing their ability to learn from the intervention; (2) participants returning to dialysis following a failed renal transplant; and (3) comorbid serious illness as defined by the treating physician. Individuals who are seeking a mental health professional or taking psychotropic medications will not be excluded from participating.

Power was calculated to detect a medium effect size of *d* = 0.40 using a sample size formula comparing time-averaged differences for continuous outcomes in repeated measurement studies [27]. The power calculations assumed the following: (a) two primary outcome measures (HADS anxiety and depression severity scores); (b) four assessment points (i.e. baseline, 3, 6, and 12 months); (c) a between-repeated measures ρ = 0.70; (d) a study-wide type I error of 0.05 (i.e. a single test α of 0.05 ÷ 5 or 0.01); (f) a type II error rate (β) of 0.20 (power of 0.80); and (g) two-tailed statistical tests. The within-subject correlation (0.70) was based upon a previous OHP trial that demonstrated high correlations over time [22]. The power analysis indicated that 38 participants would be required in each group. Allowing for an attrition rate of 20 %, a total of 96 participants, or 48 in each arm, will be recruited.

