### Statistical analyses

Intention-to-treat analysis will be employed to prevent overestimation of intervention efficacy. Categorical variables will be analysed using chi-squared tests (or Fisher’s exact test for small samples). A mixed-effects model, repeated measures (MMRM) approach will be used to examine the longitudinal profile of the two primary outcome measures at the three time points (3, 6 and 12 months post-baseline). For all MMRM analyses, baseline scores will be used as covariates and the models will include prespecified fixed effects of treatment, clinician and time, in addition to treatment-by-time and treatment-by-clinician interactions. Appropriate adjustments for multiple primary (depression and anxiety) tests will be made, i.e. Bonferroni correction to ensure the risk of type I error is maintained at 5 %. The potential impact of any additional care received by some participants will be assessed in a separate regression analysis using analysis of covariance.

Secondary analyses using analysis of covariance will be conducted to compare change scores during treatment and follow-up points for primary, secondary and process outcomes using the fixed, continuous covariate of baseline score as well as the categorical fixed effects of treatment group, clinician and treatment-by-clinician interactions. Following this, all secondary outcome measures will be assessed, as per above using first a MMRM and then assessing change scores.

Although the attrition rate is not expected to vary by group (intervention vs usual care), we will attempt to identify key predictors of attrition status (i.e. demographic or clinical baseline characteristics) and test for differences between groups. Assuming the data are missing at random, several procedures offer effective approaches that may attenuate attrition. For example, multiple imputation procedures that utilise the expectation-maximization (EM) algorithm with bootstrap estimates of standard errors will be used. A maximum likelihood model with time as a random variable will allow the use of all available data from all assessments, reducing bias and increasing power [40]. Application of these procedures has been shown to provide unbiased estimates, even in the face of substantial missing data [41].

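### The 38 per group does not follow from the power inputs printed with it; those inputs give 114 per group, and power should be restated for the planned baseline-adjusted analysis

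*Protocol article*

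**What the plan says.** The Participants section gives the whole calculation in one paragraph. The target effect comes first: "Power was calculated to detect a medium effect size of *d* = 0.40". The article then names its method: "using a sample size formula comparing time-averaged differences for continuous outcomes in repeated measurement studies". A lettered list of assumptions follows. For the endpoints it has "two primary outcome measures (HADS anxiety and depression severity scores"). For timing it has "four assessment points (i.e. baseline, 3, 6, and 12 months"). For the correlation it has "a between-repeated measures ρ = 0.70". For the error rate it has "a study-wide type I error of 0.05 (i.e. a single test α of 0.05 ÷ 5 or 0.01"). Power is set at 80%, with two-sided testing. The result follows: "The power analysis indicated that 38 participants would be required in each group". With 20% attrition this becomes 48 per arm and 96 in total.

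The Statistical analyses section describes a different analysis. A mixed model for repeated measures will "examine the longitudinal profile of the two primary outcome measures at the three time points (3, 6 and 12 months post-baseline"), with the baseline score as a covariate. The fixed effects are treatment, clinician, time, treatment-by-time and treatment-by-clinician. A Bonferroni correction is planned for the two primary tests, depression and anxiety.

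**The concern.** The article prints the method, every input the method needs, and the answer, so a reader can check the answer directly. It fails by a factor of three. The recruitment target of 96 rests on that sentence, and a null result would be read against a claim of 80% power at alpha 0.01 that the described calculation does not support.

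Two further mismatches sit in the same paragraph.

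- **Baseline as an outcome time.** The calculation counts baseline among the four outcome times. Randomisation makes the expected difference at baseline zero, so a constant difference of 0.40 cannot hold there. The planned model uses baseline as a covariate and only three follow-ups as outcomes.
- **Per-test alpha.** The calculation divides 0.05 by five, although it lists two primary outcomes and the analysis section corrects for two.

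**Working it through.** **Inputs** (Participants section): d = 0.40 with SD 1, m = 4, rho = 0.70, two-sided alpha 0.01, power 0.80. All results use the normal approximation.

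**1. The plan's own calculation.** For a time-averaged difference,

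n per group = 2 (z_alpha + z_beta)² × [1 + (m − 1) rho] / (m d²).

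The variance factor is (1 + 3 × 0.70)/4 = 0.775, so

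n = 2 × (2.576 + 0.842)² × 0.775 / 0.16 = 113.1, or 114 per group. The stated 38 is not reproduced.

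**2. Changing one input at a time.**

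| Change | n per group |
|---|---|
| None (as printed) | 114 |
| Alpha 0.025 (two primary tests) | 93 |
| Alpha 0.05 (no multiplicity correction) | 77 |
| m = 3 at alpha 0.01 | 117 |

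With everything else as printed, 38 per group would need rho of about 0.01, or d of about 0.69.

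**3. Power of 38 per group by the described formula.** The standard error is √(2 × 0.775/38) = 0.202, and 0.40/0.202 = 1.98. Power at alpha 0.01 is Φ(1.98 − 2.576), about 28%. It is 40% at 0.025 and 51% at 0.05.

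**4. Attrition.** 38/0.8 = 47.5, so 48. This step is right; the fault lies in the 38.

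**5. The planned type of analysis.** Take the average of 3, 6 and 12 months, adjusted for baseline. Assume that rho also holds between baseline and each follow-up, and ignore the clinician terms. The variance factor is (1 + 2 rho)/3 − rho².

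- At rho = 0.70 it is 0.80 − 0.49 = 0.31. The required n per group is 45.3 (46) at alpha 0.01 and 36.8 (37) at 0.025.
- At rho = 0.50 it is 0.667 − 0.25 = 0.417.
- For the 12-month difference alone at rho = 0.70 it is 1 − 0.49 = 0.51.

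Power for d = 0.40 is Φ(0.40/√(2 × factor/n) − z_alpha):

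| Contrast | rho | n per arm | Alpha 0.01 | Alpha 0.025 |
|---|---|---|---|---|
| Average of 3 follow-ups | 0.70 | 38 | 71% | 81% |
| Average of 3 follow-ups | 0.70 | 48 (full data) | 83% | 90% |
| Average of 3 follow-ups | 0.50 | 38 | 55% | 68% |
| 12 months only | 0.70 | 38 | 45% | 58% |

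The two lower entries at alpha 0.01 are Φ(2.701 − 2.576) = Φ(0.125) and Φ(2.441 − 2.576) = Φ(−0.135).

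**The case against.** Four objections deserve an answer.

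**The printed list may be incomplete.** The assumptions are lettered (a) to (d), then (f) and (g), so an item (e) may have been lost, and the source cited for the formula is not at hand. This limits what can be said about the authors' working. It does not rescue the sentence, because the printed items already fix every term of the formula.

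**The 28% is not the trial's power.** This stands. A reader might infer from step 3 that the trial is grossly underpowered, or that it needs 114 per arm. The documents do not support either reading. The analysis section specifies baseline adjustment, which the formula leaves out, and under the stated correlation that raises power with 38 per arm to about 71% at alpha 0.01 and 81% at 0.025. The maximum-likelihood model is also meant to use all available data, so patients with partial follow-up would put power between the rows for 38 and 48 per arm: 71 to 83% at 0.01, and 81 to 90% at 0.025.

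**The cause is unknown.** It is tempting to say that 76 per group was read as 76 in total, since half of 76.04 (alpha 0.05) is 38.02. That is conjecture. Other departures from the text also land close: baseline adjustment with three follow-ups at two-sided 0.025 gives 37, and rho = 0 at alpha 0.01 gives 37. The article does not show which route was taken, if any.

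**Only wording would change, so the point may seem minor.** The cost is indeed small. Even so, a stated sample size and its power claim are wrong as printed. At the alpha the article itself states, 38 evaluable per arm falls short of 80% even with baseline adjustment.

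**Conclusion.** The point holds as a statement about the described calculation: the printed inputs give 114 per group, three times the stated 38, and no version that keeps two-sided alpha 0.01 with the named formula returns 38 per group. It does not show that 96 participants are too few for the planned analysis. Whether they suffice depends on three things that the sample size paragraph does not settle: which per-test alpha applies, whether the correlation of 0.70 also holds between baseline and follow-up, and whether the test is the average over follow-up or a single visit. Over those choices, power with 38 evaluable per arm runs from about 45% (12 months only, alpha 0.01) to about 81% (average of three follow-ups, alpha 0.025, rho = 0.70). The 81% is a figure for an already fixed sample size under favourable assumptions and should be labelled so.

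**What to change.** Keep 96 participants and rewrite the sample size paragraph:

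1. Reconcile the per-test alpha. Either explain the divisor of five or use 0.05/2 = 0.025, to agree with the Bonferroni correction for two primary tests in the Statistical analyses section.
2. Replace the four-assessment calculation with one for the baseline-adjusted average of 3, 6 and 12 months. Report about 71% power at alpha 0.01, or about 81% at 0.025, with 38 evaluable per arm. If all 48 per arm contribute full data, the figures are about 83% and 90%.
3. State the conditions: d = 0.40, rho = 0.70 between baseline and follow-up as well as among follow-ups, and clinician terms ignored. Give the sensitivity figure of about 68% at rho = 0.50 and alpha 0.025.
4. State that these figures are for a time-averaged contrast, and that the 12-month contrast alone has about 58% power at 0.025.
5. Delete the claim that 38 per group follows from alpha 0.01 and four assessments. If a lettered assumption was lost from the list, restore it.

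The cost is a revised paragraph, with no extra patients and no change to study procedures.

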### Study procedures

#### Consent

The process of consent will be in accordance with the Declaration of Helsinki. All eligible participants will be fully informed that they are being asked to participate in an RCT. The procedures involved in the study, and the chances of being assigned randomly to one of two groups will be explained verbally and via an information sheet approved by St Vincent’s Hospital Human Research Ethics Committee. A signed consent form will be obtained from each participant. Participants will be made aware of their right to withdraw from the study at any time with no impact on usual clinical care received.

#### Randomisation and blinding

Following the initial screening and gaining of consent, participants will be allocated to either intervention or control group via a computer-generated block randomisation sequence created by an independent person not directly involved in the study. Due to the nature and length of the intervention, it is not possible to blind either patient or investigator to the intervention allocation.

#### Recruitment

Potential participants will be identified by dialysis clinical staff based on diagnosis and inclusion criteria and provided with a flyer and verbal explanation. Study fliers, including contact details for the research team, will also be posted online through community organisations. Participants from the community may contact researchers directly to request further information. If agreeable, patients will be informed and formally consented by a research assistant (not associated with the patient’s treatment team) and allocated to either the intervention or control group. CONSORT procedures will be followed throughout the study to ensure the minimum set of recommendations for reporting randomized trials [28]. Participants will be recruited over a 24-month period (see Fig. 1).

**Fig. 1 Fig1:**
[figure not shown]
Flowchart of the Dialysis Optimal Health Program (DOHP) randomized controlled trial (RCT)

### Intervention: DOHP

The DOHP is delivered in nine (8 + 1 booster session) sequential sessions based on a structured workbook. The workbook is central to learning, (i) providing detailed information on the contents of each session and (ii) acting as a health journal where participants can record key dates, appointments, contacts and medication details. Participants are encouraged throughout the program to identify areas of kidney disease or specific concerns upon which they would like to focus. Sessions are approximately 1 hour in duration and held weekly, apart from the ‘booster’ session, which is held 3 months after session 8. Each participant will be allocated to one OHP trained facilitator who will administer the suite of questionnaires, taking approximately 25 minutes to complete, and conduct the intervention. Learning is cumulative with each session designed to build on the previous session including tasks to complete between sessions, such as coping strategies (e.g. breathing exercises).

As the DOHP adopts a holistic collaborative care approach it is not the intention to prevent or treat depression directly, but rather to identify the impact it has on the psychosocial health of patients undergoing dialysis as per the nine sessions as outlined below. In summary, session 1 introduces the DOHP within the six domains of ‘optimal health’; considering the balance of mental, emotional, social, occupational, physical and spiritual needs of a person. This session provides participants with the opportunity to explore and understand their dialysis self-management behaviour from a holistic perspective. Sessions 2 and 3 initiate development of a health plan exploring the implications and potential complications of renal failure and dialysis in terms of strengths and vulnerabilities in session 2, and understanding and monitoring disease impact in session 3 (e.g. the effects of stress on high blood pressure). The focus of session 4 is on metabolic monitoring and medication management (e.g. blood pressure medication and low potassium diet). Session 5 expands the health plan to include key renal failure treatment partnerships and supports in the community and online (e.g. other patients, family, online forums). Session 6 focuses on change enhancement in terms of understanding past events and establishing new proactive avenues for change. The aim of session 7 is goal setting via creative problem solving and planning around the complexities of renal failure and dialysis. Session 8 strategises wellbeing maintenance and sustainability related to the dialysis treatment. The objective of the ‘booster session’ (session 9) is to consolidate progress via reviewing health plans and reflecting on achievements made toward health-related goals. An additional table provides further detail of sessions including behaviour change techniques (see Additional file 1).

A health professional (e.g. nurse, psychologist) trained in the collaborative therapy approach (2-day workshop plus regular supervision and fidelity checks) will facilitate each session. The facilitator will draw on CKD/ESKD-specific information in concordance with individual circumstances. Examples include coping strategies for addressing anxiety related to self-monitoring of blood pressure, availability of community supports, and dealing with the stress of adapting to ESKD and initiating dialysis. Emphasis is placed on the collaboration between facilitator and participant to achieve goals that stem from the participant’s intrinsic concerns and needs. Health promotion is also a major focus, hence the facilitator will encourage participants to identify early warning signs of stress and illness and integrate healthy coping strategies to prevent the build-up of stress. In conjunction with the multidisciplinary team, facilitators will coordinate visits and discuss and arrange referrals to other services depending on participant needs. Further, if at any time during the study a participant identified severe anxiety and/or depression or suicidal ideation they will be contacted by a senior clinician of the research team and where relevant, referred to an appropriate mental health service. Patient participation may be discontinued based upon self-request and/or feedback from the referred treating mental health service. Participants residing in rural and regional areas will have the option of participating in sessions via telephone or Skype (depending on patients’ access to the internet).

### Standard care

Participants randomised into the standard care condition will receive medical care consistent with patients who have ESKD. This will include regular medical appointments with medical staff, diagnostic tests (e.g. blood glucose levels) and access to treatments based upon disease status and recommendations by treating hospital staff.

### Outcome measurements

Primary and secondary outcomes will be assessed at baseline, 3, 6 and 12 months (see Table 1). Primary measures are changes in symptom severity of anxiety and depressive disorders as assessed by the Hospital Anxiety and Depression Scale (HADS) [29]. Secondary measures are: quality of life, as assessed via a disease-specific measure the Kidney Disease Quality of Life (KDQoL) [30] and health-related quality of life as assessed by the Assessment of Quality of Life (AQoL-6D) [25] and European Quality of Life-5 dimensions (EQ-5D-3L) [26] (both scales are highly cited, AQoL with Australian norms allowing comparison); self-efficacy measured by the General Self-Efficacy Scale (GSE) [31], a general sense of perceived self-efficacy in regarding daily hassles as well as adaptation to stressful life events; illness perceptions measured by the Brief Illness Perception Questionnaire (Brief-IPQ) [32], an assessment of cognitive and emotional representations of illness; coping strategies as measured by an abbreviated version of the COPE Inventory [33], the Brief COPE [34]; a 10-item measure of the Big Five personality dimensions [35]; and impact of a person’s mental health difficulties on their ability to function via the Work and Social Adjustment Scale (WSAS) [36]; treatment expectancy and rationale credibility in clinical studies as assessed by the Credibility/Expectancy Questionnaire (CEQ) [37]; perceived acceptability of treatment, assessed using the Treatment Evaluation Inventory-Short Form (TEI-SF) [38]; clinical indices such as albumin and haemoglobin levels and Kt/V (dose of dialysis); and health care utilisation for economic evaluation purposes assessed by the Health Care Utilisation Questionnaire (HCUQ) [39]. Scoring and interpretation of all questionnaires will be undertaken using the recommended published procedures outlined by the relevant questionnaire authors. Adherence to the intervention will be recorded in sessions 2 to 9 by the program facilitators as participants provide feedback on their uptake of the DOHP in the time between each session.

**Table 1 Tab1:** Primary and secondary outcome assessments and time points for Dialysis Optimal Health Program (DOHP)

Assessment tools	Baseline	3-month	6-month	12-month
Primary outcomes				
HADS (14 items)	X	X	X	X
Secondary outcomes				
AQoL-6D (20 items)	X	X	X	X
Brief COPE (28 items)	X	X	X	X
Brief-IPQ (9 items)	X	X	X	X
CEQ (6 items)		X		
Clinical indices (e.g. Kt/V)	X	X	X	X
EQ-5D-3L (6 items)	X	X	X	X
GSE (10 items)	X	X	X	X
HCUQ (17 items)	X	X	X	X
KDQoL (24 items)	X	X	X	X
TEI-SF (9 Items)				X
TIPI (10 items)	X			
WSAS (5 items)	X	X	X	X

*HADS* Hospital Anxiety and Depression Scale [29], *AQoL-6D* Assessment of Quality of Life-6 Dimensions [25], *Brief COPE* [34] abbreviated version of the COPE Inventory [33], *Brief-IPQ* Brief Illness Perception Questionnaire [32], *CEQ* Credibility/Expectancy Questionnaire [37], *EQ-5D-3 L* European Quality of Life-5 Dimensions-3 Levels [26], *GSE* General Self-Efficacy Scale [31], *HCUQ* Health Care Utilisation Questionnaire [39], *KDQoL* Kidney Disease Quality of Life [30], *TEI-SF* Treatment Evaluation Inventory-Short Form [38], *TIPI* Ten-Item Personality Inventory [35], *WSAS* Work and Social Adjustment Scale [36]

Regarding outcome measurement for the cost-effectiveness analysis the utility measurements of generating quality of life will be assessed using AQoL-6D [25] developed in Australia and the EQ-5D [26]. Regarding cost, health care utilisation of the patient will be collected from the medical records at St Vincent Hospital for inpatient use (patient consent obtained) and by self-administered Health Care Utilisation Questionnaire (HCUQ) [39] for inpatient use other than St Vincent Hospital and all outpatient and community health care use from the patient at baseline and each of the follow-up visits. The sources of the price information are from MBS (Medical Benefit Schedule), PBS (Pharmaceutical Benefit Scheme) and other Australian governmental documents. Both healthcare outcomes and costs will then be compared between participants in intervention and control groups using the incremental cost-utility ratio which indicates the incremental cost per QALY (quality-adjusted life year) of this intervention within the trial period. The estimated long-term (lifetime) impact on cost and effectiveness of the intervention beyond the trial period will be extrapolated using Markov process modelling. The Markov process model will be constructed in reflecting the evolving and progressing of the health state of patients with CKD and ESKD, including the health state of, for example, relapse of depression and anxiety. Appropriate sensitivity analysis for the best and worst scenarios will also be performed based on key variables such as the probabilities of relapse of depression and anxiety to examine the robustness of the cost-effectiveness result.

Due to variability of usual care in the control group, key aspects of standard care will be assessed via responses to the HCUQ [39]. Medical records will also be accessed to confirm diagnostic information, inpatient, outpatient and emergency department visits.

